### 5.2.3. HANDLING OF MISSING DATA

#### **Missing data for environmental exposures**

To determine whether a participant has 'ever' been exposed to an environmental exposure such as smoking or pets, missing values will be treated as '0' (no), provided that the participant responded 'no' in any completed questionnaires and that the baseline and five-year questionnaires are complete. This relies on the assumption that it is unlikely that a household member will become a smoker and then stop again, and similarly it is unlikely that the household will acquire a dog or cat for a short period of time.

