#### **Multiple Imputation**

The primary analysis will be an intention-to-treat analysis. It is already known that the proportion of missing data for the primary outcome will be more than 5%, due to loss to follow-up. To adjust for this selection bias (collider stratification bias), multiple imputation models will be conducted for the outcome variables and 50 completed data sets will be imputed by chained equations including all the children initially randomised. The primary outcome, strata variable (mode of birth: vaginal/caesarean), and the variables associated with either remaining in the study or asthma listed below will be included in the imputation model. Although there are two other randomisation strata (study site and singleton/twin), the number of participants recruited at study sites other than the Mercy, and the number of twins, is so small that it is not possible to multiply impute separately for these strata.

The directed acyclic graph (DAG) below summarizes the expected associations between variables, including the open front door path created by restriction on the collider 'remain in the study' caused by loss to follow-up and incomplete data. The multiple imputation aims to impute the missing data for those who did not remain in the study. By including variables that are expected to be associated with both remaining in the study and the outcome, the restriction on 'remain in the study' is removed and this open path is closed.

[figure not shown]

Informed by the DAG, and in order of priority, the variables listed below may be included in the multiple imputation. If necessary, the number of categories included in categorical variables will be reduced to allow the multiple imputation to run.

| Variable                        |                        | Definition                                                                                                                                                                                    |
|---------------------------------|------------------------|-----------------------------------------------------------------------------------------------------------------------------------------------------------------------------------------------|
| Maternal education              | Generated, categorical | Three categories – below year 10, year 12/trade certificate or university educated.                                                                                                           |

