| Daycare attendance  | Generated, binary      | Positive if the participant had a sibling in daycare at birth or during the first year of life, or if the participant attended any daycare in the first year of life.                         |
| Smoke exposure      | Generated, binary      | Positive if mother smoked in pregnancy or if there was ever a smoker living in the house on any questionnaire. Negative, if there is no evidence of smoking at any time point (no or missing) |
| Sex                 | Raw, binary            | Assigned male or female at birth                                                                                                                                                       |

|                                                                                                 |                        |                                                                                                                                                                                                                                                                                |
|-------------------------------------------------------------------------------------------------|------------------------|--------------------------------------------------------------------------------------------------------------------------------------------------------------------------------------------------------------------------------------------------------------------------------|
| Breastfeeding duration                                                              | Generated, categorical | No breastfeeding, <1 week, 1 wk – 3 months, 3-6 months, 6-12 months, >12 months                                                                                                                                                                                                |
| Family history of asthma                                                            | Generated, binary      | Positive if mother, father or sibling has asthma                                                                                                                                                                                                                               |

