| Timing of recruitment                                                                           | Generated, categorical | Categories determined based on date of recruitment.                                                                                                                                                                                                                            |
| Evidence of asthma                                                                 | Generated, binary      | Positive if parent reported asthma or wheeze disturbing sleep or exercise at 36 or 48 months or said yes on the follow-up questionnaire. Negative if completed the 36 and 48 month questionnaires and did not report those symptoms or said no on the follow-up questionnaire. |
| Hospitalisation for bronchiolitis in the first year of life                        | Generated, binary      | Positive if parent reports hospitalisation for bronchiolitis in the first year of life. Negative if all 3 month, 6 month, 9 month and 12 month questionnaires were complete and no hospitalisation for bronchiolitis was reported.                                             |
| Atopy (eczema  or atopic sensitization  ) at one year of age | Generated, binary      | Positive if positive for either eczema or atopic sensitisation at one year of age. Negative if negative for both eczema and atopic sensitisation at one year of age.                                                                                                           |

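### Imputation auxiliaries in SAP 5.2.3: missing smoke exposure is coded unexposed against the section's own rule, and the only earlier asthma measure is 14th of 16, optional and ambiguously defined

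*SAP*

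**What the plan says.** The Multiple Imputation part of SAP 5.2.3 plans that "50 completed data sets will be imputed by chained equations including all the children initially randomised". On which variables enter, it first says that "the variables associated with either remaining in the study or asthma listed below will be included in the imputation model", then "Informed by the DAG, and in order of priority, the variables listed below may be included in the multiple imputation". If the model will not run, the only stated remedy is to merge categories.

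The table has 16 rows. Three matter here.

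- **Smoke exposure (row 3).** It is positive for smoking in pregnancy or a household smoker on any questionnaire. Otherwise: "Negative, if there is no evidence of smoking at any time point (no or missing". The part of 5.2.3 on environmental exposures names smoking as an example and lets a missing value count as no only "provided that the participant responded 'no' in any completed questionnaires and that the baseline and five-year questionnaires are complete".
- **Evidence of asthma (row 14).** One rule makes the variable positive: "Positive if parent reported asthma or wheeze disturbing sleep or exercise at 36 or 48 months or said yes on the follow-up questionnaire". A separate rule, with no order between the two, makes it negative: "Negative if completed the 36 and 48 month questionnaires and did not report those symptoms or said no on the follow-up questionnaire".
- **Maternal education (row 1).** The categories are given as follows: "Three categories – below year 10, year 12/trade certificate or university educated".

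Under SAP 4.1.3 and 4.2, a 'no' on the 7-10-year follow-up makes the primary outcome negative, while a 'yes' leaves it missing. SAP 5.3 plans a sensitivity analysis that re-runs the regression without follow-up data. It does not mention this auxiliary.

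**The concern.** Imputation corrects for loss to follow-up only as far as its auxiliaries carry information about the missing outcomes. Three features of the table work against that.

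First, smoke exposure is forced to a value where it is unknown, and it is unknown mainly in the children whose outcomes must be imputed. Misclassification therefore tracks missingness, although chained equations could have imputed the value.

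Second, the variable closest to the outcome is near the bottom of a priority list, below season of birth, pets and paternal age, and the text leaves open whether it must be used.

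Third, that variable cannot be coded uniquely. Two programmers could code the same child differently, and could differ on whether follow-up answers remain in it for the analysis meant to exclude them.

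**Working it through.** **Rank.** The rows in order are maternal education, daycare, smoke exposure, sex, breastfeeding, family history, pets, delivery mode, season, maternal age, paternal age, low birthweight, timing of recruitment, evidence of asthma, bronchiolitis admission, atopy. Evidence of asthma is 14th of 16. Family history concerns relatives. Bronchiolitis and atopy are risk markers, not asthma.

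**Smoke exposure.** From SAP 2.1, 1,272 − 1,027 = 245 children (245/1,272 = 19.3%) did not consent to Part 2 and lack its questionnaires. The environmental-exposure rule would not allow missing = no for them. The table codes them negative unless smoking was already reported. The SAP gives no smoking rates, so these are assumptions:

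- Ever exposed 20%, reported before leaving 12%: 1 − 12/20 = 40% of exposed leavers miscoded, or 245 × 0.08 ≈ 20 children.
- 15% and 12%: 1 − 12/15 = 20%, or 245 × 0.03 ≈ 7 children.
- 25% and 15%: 1 − 15/25 = 40%, or 245 × 0.10 ≈ 25 children.

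**Evidence of asthma.** The SAP gives no rates for this either. Assumed:

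- true risks 22% and 16% (the SAP 2.4 planning values), so a difference of 6 points
- a fraction m of five-year answers missing, unrelated to asthma
- a fraction f of those children answering the follow-up truthfully
- 36/48-month symptoms with sensitivity 0.70 and specificity 0.85, known for 90% of five-year responders and 40% of the rest
- each arm imputed separately, with no other auxiliary

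Without the auxiliary, the estimated risk in an arm is p(1−m) / [p(1−m) + (1−p)(1−m+mf)]. With m = 0.3 and f = 0.4:

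- 22% arm: 0.154/(0.154 + 0.78 × 0.82) = 0.154/0.7936 = 19.4%
- 16% arm: 0.112/(0.112 + 0.84 × 0.82) = 0.112/0.8008 = 14.0%
- difference: 5.42 points

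With the auxiliary, the 2×2 table of outcome by auxiliary is fitted by EM. Each incomplete record is spread over its compatible cells in proportion to the current fit, until stable. This is the value that multiple imputation under that model targets. The SAP column lets the positive rule win where both rules apply.

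| m | f | Auxiliary as in SAP | 36/48 months only | None | Cost of omission |
|---|---|---|---|---|---|
| 0.2 | 0.4 | 5.90 | 5.71 | 5.65 | 0.25 |
| 0.2 | 0.6 | 5.85 | 5.57 | 5.49 | 0.36 |
| 0.3 | 0.4 | 5.82 | 5.52 | 5.42 | 0.40 |
| 0.3 | 0.6 | 5.75 | 5.31 | 5.17 | 0.58 |
| 0.4 | 0.4 | 5.73 | 5.29 | 5.14 | 0.59 |
| 0.4 | 0.6 | 5.62 | 4.99 | 4.79 | 0.83 |

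If the negative rule wins instead, the SAP column falls by 0.04 to 0.06.

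**Sensitivity analysis.** With a five-year-only outcome and follow-up answers left in the auxiliary, the difference is 6.08 to 6.24 if the positive rule wins and 6.02 to 6.07 if the negative rule wins. With a 36/48-month-only auxiliary it is 6.00.

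**The case against.** Four stronger readings are tempting. The SAP supports none of them.

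- **All children lost to follow-up are called unexposed.** Smoking in pregnancy, or on any questionnaire completed before leaving, still counts as positive. The error is confined to smoking that was never reported or that began later, and 5.2.3 itself treats temporary household smoking as unlikely.
- **Evidence of asthma will be dropped.** No rule drops it. Merging categories leaves a binary variable untouched, and the order is said to rest on a DAG that is not visible here. What stands is that 'will' and 'may' conflict, and that an order of priority has little purpose unless lower rows can be left out.
- **The sensitivity analysis keeps follow-up data.** SAP 5.3 excludes those data without limiting the exclusion to the outcome, and a natural reading is that the data are re-imputed. The SAP is silent on this; it does not say otherwise.
- **Reuse of follow-up answers contaminates the primary analysis and should be removed.** A child with a follow-up 'no' has an observed outcome and is not imputed. A 'yes' reaches the analysis only through this auxiliary. Taking follow-up data out moves every row of the table further from 6.

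It is also fair that most of the bias comes from the one-sided outcome rule and not from this list. The 36/48-month answers alone recover only 0.06 to 0.20 points (column four minus column five). The 245 children outside Part 2 would have no such answers.

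**Conclusion.** The concern holds as a set of partial mis-specifications that should be corrected before unblinding.

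The smoking contradiction is plain from the text and needs no assumption. Its effect on the risk difference was not calculated and is probably small, since smoking is one moderate risk factor among many.

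The rank of evidence of asthma does harm only if the variable is left out. The cost is then about 0.3 to 0.8 of 6 points. That range rests on the assumed rates, on five-year answers missing independently of asthma, and on a comparison with no auxiliary at all, so other rows in the model might reduce it somewhat.

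The undefined precedence is certain from the text and moves the estimate by about 0.05 points. Silence on the auxiliary in the sensitivity analysis is worth at most about 0.2 points under the same assumptions. The missing category for mothers who left school after year 10 or 11 is a wording correction with no shown effect.

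**What to change.** In SAP 5.2.3 and 5.3:

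1. **Smoke exposure.** Apply the environmental-exposure condition, and otherwise leave the value missing and impute it. Alternatively, use only smoking in pregnancy and in the household at birth.
2. **Evidence of asthma.** Put it first and make it mandatory. Replace the will/may conflict with one statement of which variables are compulsory and how any others are dropped.
3. **Precedence.** State which rule wins when 36- or 48-month symptoms meet a later follow-up 'no'.
4. **Sensitivity analysis.** State that it rebuilds evidence of asthma from the 36- and 48-month questionnaires only and re-imputes before the regression is re-run.
5. **Primary analysis.** Keep follow-up answers in this auxiliary while the 'no'-only outcome rule of SAP 4.1.3 and 4.2 stands. If that rule changes, change both together.
6. **Maternal education.** Reword the categories so that years 10 and 11 have a place.

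The cost is edits to one table and two paragraphs, and one re-run of the imputation. No new data are needed. SAP 5.1 defers full unblinding until the SAPs are final, so the edits belong before that point.

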#### 5.2.4. SUBGROUP ANALYSIS

Additional adjusted models will be estimated to explore the potential heterogeneity of the effect of the intervention. Each model will include as covariates the mode of birth stratification factor, and an interaction term estimating the interaction between the intervention and the sub-group variable (listed below). Where the models provide evidence that the intervention varies between sub-groups, the intervention effect in each sub-group and their 95% confidence intervals will be

presented, together with the p-value for the intervention-by-subgroup interaction, as a guide to the strength of the evidence for an interaction. All sub-group analysis will be conducted on the imputed data.

Sub-groups are variables that are known or suspected risk factors for asthma in childhood that are also known or suspected to influence the immune response to BCG vaccination. Sub-group analysis will include:

1. Either parent has a history of asthma
2. Sex
3. Maternal history of BCG vaccination

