## 2. BACKGROUND/INTRODUCTION

### 2.1. STUDY DESIGN

MIS BAIR is a phase III, randomised, controlled trial in infants to determine if the bacille Calmette-Guérin (BCG) vaccine reduces the incidence of eczema, allergies, infections and asthma in the first five years of life.

Infants were recruited at Mercy Hospital for Women, Werribee Mercy, Geelong Hospital, St John of God and Murdoch Children's Research Institute in Melbourne over a three-year period from August 2013 to September 2016. At trial design we planned to randomise 1,438 infants 1:1 to receive the BCG vaccine or no vaccine. However, recruitment to the study was stopped before this number was reached as the BCG-Denmark vaccine became unavailable due to a worldwide shortage. The actual number randomised was 1272. Infants were randomised within ten days of birth.

The study involved two parts:

Part 1 – From birth to one year of age

Part 2 – From one to five years of age

At the 1-year MIS BAIR visit participants were asked to re-consent if they wished to continue into Part 2 of the study. For those families who had not been consented at the 1-year MIS BAIR visit, had not verbally declined participation and had given consent to be contacted for future studies, an invitation letter and the PICF were sent to them by email, post or through REDCap and they could consent by post, on REDCap or in person (e.g. at a study visit). Of the 1272 in Part 1, 1027 consented to continue into Part 2.

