## 2.3. STUDY POPULATION

1,272 healthy newborns were randomised, within 10 days of birth, in a 1:1 ratio, to study group 1 (BCG, n=637) or study group 2 (no BCG, n=635). Twin pairs were randomised to the same group but only one twin from each pair was included as a study participant, regardless of birth order. A total of 21 sets of twins were randomised in the trial and 17 sets of twins continued into Part 2.

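### Sub-group effects and interaction p-values are presented only where the models show evidence of interaction, by no stated criterion, so reporting depends on the result and displayed contrasts are inflated on average

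*SAP*

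**What the plan says.** SAP section 5.2.4 sets the purpose as exploratory: "Additional adjusted models will be estimated to explore the potential heterogeneity of the effect of the intervention". Each model contains birth mode and a treatment-by-sub-group interaction. Three variables are listed: parental history of asthma, sex, and, last on the list, "3. Maternal history of BCG vaccination". The data set is also fixed: "All sub-group analysis will be conducted on the imputed data".

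The reporting rule opens with a condition: "Where the models provide evidence that the intervention varies between sub-groups, the intervention effect in each sub-group and their 95% confidence intervals will be" shown. Later in the same sentence the interaction p-value is attached to that display: "together with the p-value for the intervention-by-subgroup interaction, as a guide to the strength of the evidence for an interaction". On the natural reading, the sub-group estimates, their intervals and the interaction p-value all fall under the opening condition. The SAP does not define what counts as evidence, here or elsewhere, and does not commit to showing a sub-group for which evidence is judged absent. By contrast, sections 5.3 and 5.4 present the primary and secondary comparisons without any such condition.

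**The concern.** There are two separate defects.

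- **Discretion.** Because evidence is undefined, whether a sub-group appears can be settled only after its result is known.
- **Selection.** Even with a fixed threshold, showing a contrast only when it looks large makes the displayed contrasts too large on average, and most of all when power is low. Naming a threshold would cure the first defect and leave this one.

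The rule also sits awkwardly with its own purpose. A p-value meant to guide the reader on the strength of evidence cannot do so if it appears only after evidence has been accepted.

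At stake is how readers judge whether any BCG effect on asthma differs by parental asthma, sex or maternal BCG history. They could see one striking contrast without the unremarkable ones needed to put it in proportion.

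**Working it through.** The SAP states no figure for the sub-group analysis, so there is nothing to reproduce. The check asks what the rule would do under plausible readings.

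**Inputs from the SAP**
- Three sub-group variables (section 5.2.4).
- 1:1 allocation (section 2.3).
- Number of children (section 2.1): "The actual number randomised was 1272" as the upper figure, since imputation includes all randomised children. The lower figure comes from "Of the 1272 in Part 1, 1027 consented to continue into Part 2", since imputation does not restore full information.
- Asthma ever, 22% versus 16%, a 6-point design effect (section 2.4).

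**Assumptions, because the SAP is silent**
- Display thresholds of p<0.05, 0.10 or 0.20.
- One outcome (section 5.2.4 does not say which outcomes the sub-group models cover) and independent tests.
- A 50:50 sub-group split, with 30:70 as a variation.
- A true interaction of either zero or 6 points, the latter as large as the whole design effect.
- No imputation noise.

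**Step 1. Chance of displaying at least one of three sub-groups when none differs**
- p<0.05: 1 − 0.95³ = 14.3%
- p<0.10: 1 − 0.90³ = 27.1%
- p<0.20: 1 − 0.80³ = 48.8%

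The unstated threshold changes this more than threefold.

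**Step 2. Precision of the interaction**

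Variance term: 0.22×0.78 + 0.16×0.84 = 0.1716 + 0.1344 = 0.306. With equal halves, the standard error of the difference between two sub-group risk differences is twice the overall standard error.
- N=1,027 (about 513 per arm): √(0.306/513) = 0.0244; doubled, 0.0488, or 4.9 points.
- N=1,272 (636 per arm): √(0.306/636) = 0.0219; doubled, 0.0439, or 4.4 points.

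**Step 3. Power for a true 6-point interaction at p<0.05**
- N=1,027: Φ(0.06/0.0488 − 1.96) = Φ(−0.73) = 23%.
- N=1,272: Φ(0.06/0.0439 − 1.96) = Φ(−0.59) = 28%.

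**Step 4. Average displayed contrast when the truth is 6 points** (simulation, 400,000 trials per scenario, control rate 22%, overall risk difference −6 points, 50:50 split; ratio to 6 in brackets)

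| Threshold | N=1,272 | N=1,027 |
|---|---|---|
| p<0.05 | 11.2 (1.87) | 12.3 (2.05) |
| p<0.10 | 10.2 (1.70) | 11.1 (1.85) |
| p<0.20 | 9.1 (1.52) | 9.8 (1.63) |

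With a 30:70 split the averages run from 9.5 to 12.9 points (9.5/6 = 1.58 to 12.9/6 = 2.15).

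**Step 5. When there is no true interaction** (N=1,272, 50:50)

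The mean absolute contrast is 3.5 points if always shown. Among displayed results it is 10.2, 9.0 or 7.7 points at the three thresholds. Coverage of a displayed sub-group's 95% interval falls from 95% to 66%, 75% or 83%. With a true 6-point interaction the loss of coverage is small: 92%, 94% and 95%.

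**Step 6. With the condition removed**

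In the same simulation, a true 6-point contrast is shown as 6 points on average and sub-group interval coverage is about 95%.

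**The case against.** The strongest defence is that this is a disclosed rule. The three variables, the model and the data set are fixed, and section 5.1 says full unblinding waits until all SAPs are approved and publicly available. A reader can therefore see that three analyses were planned and notice which are absent. That stands: a reader might infer concealed cherry-picking, and the document does not support it. What is lost is the estimates and intervals for the unremarkable sub-groups.

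A second defence is that using the p-value as a guide avoids a bright line on purpose. That is reasonable as interpretation, and it explains the missing cut-off. It does not help when presentation itself turns on the same judgement. The clause could be read as showing the p-value in every case, but the conditional reading is the more natural one.

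Two stronger claims are also tempting and should not be made.

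- **That every displayed effect is exaggerated.** Inflation holds on average. At p<0.20 with N=1,272, an estimate of 1.282 × 4.39 = 5.6 points would be displayed, which is below a true 6. A large true interaction, detected with high power, would be little inflated.
- **That a displayed 6-point interaction is overstated at least 1.6 times.** That bound (1.96 × 4.88 / 6) needs p<0.05, N=1,027 and a 50:50 split. At p<0.10 it is 1.645 × 4.88 / 6 = 1.34, and at p<0.05 with N=1,272 it is 1.96 × 4.39 / 6 = 1.43. The SAP sets no threshold, so no single bound follows.

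Nor does the SAP support saying that null results would be unavailable for later pooling, since it says nothing on supplementary tables or data sharing.

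**Conclusion.** The point holds: as written, section 5.2.4 makes reporting of three pre-specified exploratory sub-groups depend on their results, by an unstated criterion, and inflates displayed contrasts on average.

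The inflation is roughly 1.5 to 2 times for a true 6-point interaction with equal sub-groups, depending on threshold and N. The chance of a spurious display ranges from about 14% to 49%. These sizes depend on assumed thresholds, sub-group shares and true interaction. If the models cover more than one outcome, the chance of a spurious display would be higher. The direction does not depend on whether 1,027 or 1,272 is used.

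Severity is minor to moderate. The analyses are few, pre-specified and exploratory, and the primary and secondary comparisons are untouched.

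**What to change.** In section 5.2.4, delete the opening condition and state that, for all three sub-group variables and whatever the result, the following will be presented from the imputed data:

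- the adjusted risk difference with 95% confidence interval in each level;
- the interaction estimate with its 95% confidence interval and p-value.

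Add observed numbers and percentages by arm within each level, for description and marked as observed, since imputed counts are not single integers. Label the results as exploratory and not adjusted for multiplicity. State which outcome or outcomes the models cover. No threshold is then needed.

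The cost is a short rewording and one table or forest plot. The models are already planned.

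### All subgroup interactions are estimated on imputed data, but the imputation model omits maternal BCG history, defines family asthma differently and specifies no arm-by-subgroup terms, so a true interaction would be pulled toward zero.

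*SAP*

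**What the plan says.** SAP section 5.2.4 plans adjusted models with an intervention-by-subgroup interaction for three variables: asthma in either parent, sex, and "Maternal history of BCG vaccination". On the data set it says "All sub-group analysis will be conducted on the imputed data". Subgroup-specific effects and the interaction p-value are to be presented "Where the models provide evidence that the intervention varies between sub-groups"; no threshold is given.

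The imputation model is in SAP section 5.2.3, under Multiple Imputation. It states that "50 completed data sets will be imputed by chained equations including all the children initially randomised". Its contents are given as "The primary outcome, strata variable (mode of birth: vaginal/caesarean), and the variables associated with either remaining in the study or asthma listed below". The listed variables are optional: "in order of priority, the variables listed below may be included in the multiple imputation". There are 16 of them. Sex is one. Family history of asthma is another, coded as "Positive if mother, father or sibling has asthma". Maternal BCG history is not listed. Randomised arm and arm-by-variable terms are not named. Imputing separately is mentioned only for site and plurality, where it is ruled out because the numbers are small.

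The only sensitivity analysis, in section 5.3, concerns the follow-up questionnaire and the primary outcome. No complete-case check of the subgroups is planned.

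**The concern.** An imputation model should hold at least the structure that the analysis model will estimate. Here the analysis estimates arm-by-subgroup interactions. If the model that fills in missing outcomes has no such term, the imputed outcomes carry little of the interaction, and averaging them with the observed outcomes dilutes it. If the subgroup variable is absent altogether, as maternal BCG history is, naming arm in the model does not repair this.

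At stake is how the subgroup results would be read. A true difference in the BCG effect would be understated, with less power to detect it. Because the diluted interaction also decides whether subgroup effects are shown, the difference might not be reported. A finding of no heterogeneity would then be partly a product of the imputation.

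**Working it through.** The SAP gives no subgroup figure to reproduce, so the check is of the mechanism and its size.

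**Input from the SAP.** 1,272 children were randomised and 1,027 consented to Part 2 (section 2.1). Non-consent is (1,272 - 1,027)/1,272 = 245/1,272 = 19.3%. The SAP says only that more than 5% of primary outcomes will be missing.

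**Assumptions.** The subgroup risks, subgroup share and missing fraction f are not in the SAP. Assumed risks of asthma ever:

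| Subgroup | No BCG | BCG | Risk difference |
|---|---|---|---|
| Present | 30% | 18% | -12 points |
| Absent | 18% | 16% | -2 points |

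True interaction = -12 - (-2) = -10 points. Subgroup share is 30% or 50%, f is 19.3%, 30% or 40%, and missingness is unrelated to the outcome within cells.

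**Formula.** Estimated interaction = (1 - f) × true interaction + f × interaction carried by the imputed outcomes.

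*Subgroup variable or arm left out of the imputation model.* Without auxiliary variables, the imputed outcomes carry an interaction of 0:
- f = 19.3%: 0.807 × (-10) = -8.1
- f = 30%: 0.70 × (-10) = -7.0
- f = 40%: 0.60 × (-10) = -6.0

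This is the case of maternal BCG history even when arm is included.

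*Arm and subgroup as main effects only.* A main-effects logistic model fitted to the four cells gives imputed outcomes with a risk-difference interaction of -1.35 points (30% share) or -1.80 points (50% share):
- f = 19.3%: -8.07 + 0.193 × (-1.35 or -1.80) = -8.3 or -8.4
- f = 30%: -7.0 + 0.30 × (-1.35 or -1.80) = -7.4 or -7.5
- f = 40%: -6.0 + 0.40 × (-1.35 or -1.80) = -6.5 or -6.7

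**Check by simulation.** A separate simulation assumed a 22% risk without BCG in both subgroups, and 22% and 10% with BCG (true interaction -12 points), with outcomes missing completely at random. Share of the true interaction recovered at N = 300,000, over subgroup shares of 30% and 50%:

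| Imputation model | 20% missing | 30% missing | 40% missing |
|---|---|---|---|
| With arm-by-subgroup term | 100-102% | 98-99% | 100-103% |
| Without it | 78-81% | 66-72% | 58-63% |
| Without it, plus an early-asthma auxiliary seen in half of those missing the outcome | 80-85% | 72-76% | 61-68% |

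At N = 1,272 and a 50% share (120 replicates, 8 imputations, Monte Carlo error about 3 to 5 points), power of the interaction test was about 65% with the term and 46-48% without it at 20% missing. At 40% missing it was about 54% and 13-17%. With no true interaction, the estimate stayed near 0, and the models without the term rejected in 0-2% of replicates.

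**The case against.** A reader might infer that arm is excluded from the imputation model. The SAP does not say so: arm is not named, but it is not ruled out. If imputation were in fact done by arm, the sex interaction would be preserved provided sex is included, and the family-history interaction largely so. That part of the objection stands, and the supportable wording is that arm is not specified. It does not help maternal BCG history, which is missing from the list under either reading.

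A reader might also infer that imputed outcomes carry no effect modification at all. That is too strong. A main-effects model still carries a little on the risk-difference scale. The listed auxiliaries (evidence of asthma at 36 or 48 months, bronchiolitis admission, atopy at one year) can transmit some signal where observed, as can covariates correlated with maternal BCG history. In the simulation, one such auxiliary recovered only a few points more of the interaction.

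The family-history mismatch is the smaller part. Every child with an affected parent is also positive on the imputation variable; the two differ only where a sibling alone is affected.

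The subgroup models are described as exploratory, and the bias arises only if a true interaction exists, so false subgroup claims are not the risk. Both points limit the severity. Neither answers the mismatch between the imputation and analysis models.

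**Conclusion.** The point holds for a plan followed as written. Its firmest part is that maternal BCG history is a named subgroup but absent from the imputation list. Next come the unspecified arm and arm-by-subgroup terms, and the optional status of sex and family history. The sibling definition is a minor addition.

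Attenuation is at most about the imputed share of outcomes, so near 5% missing it would be small. The -10 point interaction is larger than the whole 6-point reduction in asthma ever (22% to 16%) cited in section 2.4, so it shows proportions and is not a forecast. The 19.3% is non-consent to Part 2, not the missing-outcome fraction: negative answers at 7 to 10 years may recover some primary outcomes, and non-response among those who consented would add to the missing.

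If arm were in fact omitted, the main effect would be diluted too. That is a separate and more serious matter for the primary analysis. The change is worth making before unblinding, at the weight due to exploratory subgroups.

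**What to change.** In section 5.2.3:
- State that randomised arm is in the imputation model.
- Make sex, maternal BCG history and asthma in either parent (mother or father, as the subgroup is defined) required variables, outside the priority list.
- Include arm-by-subgroup terms for these three variables, or impute separately by arm if the models run stably.

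In section 5.2.4:
- Report subgroup risk differences, 95% confidence intervals and interaction p-values for all three subgroups whatever the result.
- A complete-case run of the same models would be a useful check.

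Imputation by arm should be an option and not the rule. With 637 children in the BCG arm and the 16% risk from section 2.4, expected observed events are 637 × 0.16 × 0.807 = 82 at 19.3% missing and 637 × 0.16 × 0.60 = 61 at 40%, against 16 listed variables, several with more than two categories. The SAP already expects that categories may have to be merged for the imputation to run. Three interaction terms are the lighter route.

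The cost is SAP wording, imputation code, a slightly larger model and a few table rows.
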